### 3.3 Hypotheses

#### Primary Feasibility Hypothesis

The protocol of two stewardship strategies [Antimicrobial restriction and preauthorization and post-antibiotic prescription review] will receive approval at hospitals. The two stewardship strategies will both be successfully implemented, including training of local pharmacists (PharmDs), at all four hospitals.

#### Secondary Stewardship Hypotheses

1. Antimicrobial restriction and preauthorization will be less resource-intensive for hospitals (e.g., set-up time, approval time, personnel resources) than post-antibiotic prescription review (PAR) and feedback.
2. Prescribers will consider preauthorization to be intrusive to clinician autonomy and patient care.
3. The cost of performing PAR by a trained pharmacist will be offset by the cost savings achieved by decreasing antimicrobial cost.
4. Both strategies will lead to a decrease in utilization for targeted antimicrobials relative to utilization in the period prior to implementation of the stewardship strategies.
5. Decreases in targeted antimicrobial utilization from antimicrobial restriction will be offset by increases in use of alternative antibiotics.
6. The strategy of antimicrobial restriction and preauthorization will be less effective at reducing overall antimicrobial use than the strategy of prospective audit and feedback, as it will not shorten duration of antimicrobial therapy.

### 3.4 Study Objectives

#### 3.3.1 Primary objectives and outcomes

##### Feasibility Objectives

1. To evaluate having the protocol of two stewardship intervention strategies approved by hospital administration and committees
2. To evaluate the training of local PharmDs in administration of the two stewardship strategies
3. To evaluate the initiation and implementation of the two stewardship strategies at four hospitals

#### 3.3.2 Secondary Objectives and Outcomes

To estimate and compare the time required of the pharmacist to administer each strategy

1. To estimate and compare the resource utilization of each strategy, where resource utilization includes pharmacist time and cost of antibiotics.
2. To compare the days of therapy (DOT) for antibiotics of interest between each strategy

DOT will be measured as the number of days a patient receives each targeted and alternative antibiotic during the hospital admission.

3. To compare patient-specific outcomes between each strategy, including but not limited to the following:

a. Total hospital days

b. Intensive care unit admission

4. To compare the prescriber and pharmacist perceptions of the two stewardship strategies

5. To develop integrated measures of benefit: risk for AS (based on days of therapy, hospital days, and patient outcomes such as ICU admission and survival) and compare strategy effects with respect to these measures

### 3.3.3 Exploratory objective

To evaluate the interpretations reached from analysis of data based on traditional (DOT/patient-days) outcomes as compared to newer proposed outcomes (defined in Section 3.1.3 Secondary Objectives, number 5).

## 3.5 General statistical considerations

- Tables will be presented by Hospital and intervention; each of the 4 sites will be evaluated separately.
  - Stratified pooled analyses may also be conducted
- Dates will not be shown, but converted to days from intervention (intervention) or first hospital contact (feasibility).
- Each Table/Figure/Listing will be annotated with the name and location of the program used to create it, including its location directory.
- All programs that create permanent study-specific derived datasets or that contribute to analyses of the primary or secondary objectives will be validated according to CBAR SOPs
- Categorical variables will be summarized with n and proportion
- Continuous variables will be summarized with mean, sd, median, Q1, Q3, min and max.
- For secondary analyses, there are 3 contrasts of interest
  - PAR vs. historical control
  - Formulary Restriction/Preauthorization (Res/PreA) vs historical control
  - PAR vs Res/PreA
- For each contrast, the difference in outcomes will be estimated using 95% confidence intervals
  - Difference in proportion with 95% CIs for binary outcomes
  - Difference in means with 95% CIs for continuous outcomes

### 3.5.1 Cluster Randomization and Analysis

This antimicrobial stewardship study was implemented at four hospitals, where each hospital is considered a single cluster. Cluster randomized trials can be analyzed at the cluster level or the patient level. Ideally, analyses are conducted on the cluster level as this is the unit of randomization. However, we will analyze this study using the patient as the unit of analyses as there are only four clusters.

Since randomization occurs at the cluster level but analyses must be conducted at the patient level, the benefits of randomization (i.e., expectation of balance of confounding factors) cannot be assumed. The small sample size of 4 clusters may also negate the benefits of randomization. The crossover nature of the design will help to balance confounding factors as each hospital can serve as its own control. However, as the crossover occurs at the cluster level, and the patients are neither randomized nor crossed-over, it does not have the same advantages as a standard crossover trial and it does not eliminate within-patient variation; the analyses cannot be “paired”.

Since the effect of the intervention is not only a function of the intervention itself but also of the pharmacist, there is potential for considerable site variation in response. Thus each of the four sites will be evaluated separately. Stratified pooled analyses may also be conducted.

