## 4 STUDY DESIGN

This study is a three-stage cluster randomized historically controlled crossover trial designed to evaluate the feasibility of the implementation of two AS strategies. Data will be obtained from four community hospitals in three stages. In stage 1, historical data from each hospital will be collected for the year prior to study initiation from all participating hospitals. These data are used as a control representing current practice. In stage 2, the four hospitals will be divided into two pairs based upon bed size. One hospital from each pair will be randomly assigned to a six-month period of antimicrobial restriction and preauthorization (Strategy 1; stage 2) followed by a six-month period of post-antibiotic prescription review (Strategy 2; stage 3). The other two hospitals will undergo Strategy 2 in stage 2 followed by Strategy 1 in stage 3 to help alleviate the concern for seasonal/temporal effects when comparing the strategies to each other. Temporal/seasonal effects are not controlled when comparing to the historical control. A one-month wash out will be performed between each stage. Three antibiotics will be specifically targeted for intervention: anti-pseudomonal carbapenem of choice at the study hospital, vancomycin, and piperacillin-tazobactam. Utilization of alternative antimicrobials, including fluoroquinolones, cephalosporins, and anti-methicillin-resistant *Staphylococcus aureus* (anti-MRSA) systemic antimicrobials (e.g., nafcillin, daptomycin, linezolid, ceftaroline, clindamycin, and trimethoprim-sulfamethoxazole [TMP-SMX]) will also be collected.

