#### 9.4.1.3 Discussion of cluster randomized design and the key secondary analysis

This antimicrobial stewardship study will be implemented at four hospitals, where each hospital is considered a single cluster. The four hospitals participating in this study will be paired by size. One hospital in each pair will receive Strategy 1 followed by Strategy 2, while the other hospital in each pair will receive Strategy 2 followed by Strategy 1. The ordering within each pair will be randomly assigned.

Cluster randomized trials can be analyzed at the cluster level or the patient level. Ideally, analyses are conducted on the cluster level as this is the unit of randomization. However, we will analyze this study using the patient as the unit of analyses as there are only four clusters.

Since randomization occurs at the cluster level but analyses must be conducted at the patient level, the benefits of randomization (i.e., expectation of balance of confounding factors) cannot be assumed. The small sample size of 4 clusters may also negate the benefits of randomization. The crossover nature of the design will help to balance confounding factors as each hospital can serve as its own control. However, as the crossover occurs at the cluster level, and the patients are neither randomized nor crossed-over, it does not have the same advantages as a standard crossover trial and it does not eliminate within-patient variation; the analyses cannot be “paired”.

Since the effect of the intervention is not only a function of the intervention itself but also of the pharmacist, there is potential for considerable site variation in response. Thus each of the four sites will be evaluated separately. Stratified pooled analyses may also be conducted.

For each site and each contrast (Intervention 1 vs. control; Intervention 2 vs. control; and Intervention 1 vs. Intervention 2), the difference in outcomes will be estimated using 95% confidence intervals. Examples for binary and continuous outcomes are displayed in Figure 9-2 and Figure 9-3, respectively.

Figure 9-2

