#### Study Design

The study design has limitations. First, the study is essentially non-randomized. Even randomization of hospitals cannot guarantee the balance of confounding factors on the unit of analyses (patients). The cross-over design helps to alleviate this concern as each hospital would be expected to enroll similar populations into each intervention period.

Second, our designed strategies may miss intervention opportunities. Our study design includes pharmacist interventions during business hours on Monday through Friday and does not include weekend interventions. This inclusion criterion will impact Strategy 1 more than Strategy 2, as no alternative approach is available for Strategy 1. To overcome this limitation for Strategy 2, we will allow the intervention to occur within 72 hours of prescription  $\pm$  24 hours, if necessary. This window for intervention will be adequate to intervene on all antibiotic prescriptions. We believe that this approach is appropriate, as we suspect this approach is likely to mirror how most hospitals will eventually implement each of these interventions; thus, it is more likely to lead to true conclusions regarding the feasibility and outcomes of each of these interventions.

Third, the short study period and limited study sites will hinder our ability to demonstrate definitive changes in our secondary analyses, including changes in antimicrobial utilization. The primary goal of this study, however, is to assess feasibility. An additional limitation to the short study period, is that there may be temporal effect that will differ across the two study periods

Next, the effectiveness of any stewardship program is likely to vary depending on the experience and expertise of the pharmacist performing the PAR and local hospital culture.

As the primary control group is historical, subsequent comparisons may be biased by temporal effects. The crossover nature of the trial design helps to alleviate this bias inherent to comparing the AS interventions in pooled analyses.

Lastly, DOT is limited to the duration of hospitalization, which ends upon discharge or death.

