#### 6. Hospital Admissions

**Purpose:** To summarize hospital admissions over the time periods of interest.

Hospital Admissions Tables, by hospital

a. Number of unique admissions by hospital

1. In the year preceding the start of the study period 1 (October 6, 2013 through October 5, 2014)
2. Study period 1 (October 6, 2014 through April 3, 2014)
3. Study period 2 (May 4, 2015 through October 30, 2014)

b. Number of admissions by hospital that received an “Included antibiotic” or “other antibiotic”

1. In the year preceding the start of the study period 1 (October 6, 2013 through October 5, 2014)
2. Study period 1 (October 6, 2014 through April 3, 2014)
3. Study period 2 (May 4, 2015 through October 30, 2014)

c. Number of admissions by hospital that received an “Included antibiotic”

1. In the year preceding the start of the study period 1 (October 6, 2013 through October 5, 2014)
2. Study period 1 (October 6, 2014 through April 3, 2014)
3. Study period 2 (May 4, 2015 through October 30, 2014)

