408         than one intervention over the course of a year)

409 Signs and symptoms

410     • Fever

411     • Leukocytosis

412     • Hypotension

413     • Cough or Sputum production

414     • Other signs or symptoms

- 415 • List of other/specifies
- 416 • Number of signs and symptoms per intervention

417 Culture data

- 418 • Culture data available for review (yes/no)
- 419 • If yes, was the culture data reviewed
- 420 • If yes, did it help inform the recommendation?

421 Intervention outcome

- 422 • Was the recommendation followed?
- 423 • Was there an ID consult after the intervention?
- 424 • ICU admission

425 Ultimate Infection diagnosis related to recommendation

- 426 • Pneumonia
- 427 • UTI
- 428 • Meningitis
- 429 • Surgical site infection
- 430 • SSTI
- 431 • Colitis
- 432 • Bacteremia
- 433 • Sepsis with unknown source
- 434 • No infection
- 435 • Other
- 436 • List of other, specify

437 **10. Days Of Therapy**

438 **Purpose:** To address Secondary objective 2, to compare DOT for antibiotics of interest between each  
439 strategy.

440

- 441 • Days of therapy (DOT) for targeted and alternative antibiotics
  - 442 ○ Per the protocol, DOT will be measured as the number of days a patient receives
  - 443 each targeted and alternative antibiotic during the hospital admission

444 The three targeted antibiotics are:

- 445 • Anti-pseudomonal carbapenem of choice at the study hospital
- 446 • Vancomycin
- 447 • Piperacillin-tazobactam.

448 The alternative antimicrobials of interest are:

- 449 • Fluoroquinolones
- 450 • Cephalosporins
- 451 • anti-MRSA systemic antimicrobials (e.g., nafcillin, daptomycin, linezolid, ceftaroline,
- 452 clindamycin, and TMP-SMX).

Among admissions with an included antibiotic, by hospital

- Table 1
  - Year prior to study
  - Period 1 Admission with Included antibiotic, no intervention
  - Period 1 Admission with stewardship intervention
  - Period 2 admission with Included antibiotic, no intervention
  - Period 2 admission with stewardship intervention
- Table 2
  - Period 1 (all admissions with an antibiotic of interest)
  - Period 2 (all admissions with an antibiotic of interest)
- Table 3
  - For 3 contrasts (PAR vs Historical year; Res/PreA vs historical Year; PAR vs Res/PreA)
  - Difference in proportion used drug with 95%CI
  - Difference in Mean DOT with 95% CI

For each antibiotic,

- proportion of admissions where the antibiotic was received
- DOT for the antibiotic

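### By-hospital PAR vs Res/PreA contrasts are fully aliased with study period, and the period-adjusted model that could carry this comparison is neither named as the estimate nor extended beyond DOT

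*Combined protocol and SAP*

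**What the plan says.** **Level of analysis.** SAP 3.5.1 states: "Thus each of the four sites will be evaluated separately. Stratified pooled analyses may also be conducted". Protocol 9.4.1.3 has the same rule and attaches 95% confidence intervals to it: "For each site and each contrast (Intervention 1 vs. control; Intervention 2 vs. control; and Intervention 1 vs. Intervention 2".

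**Reported contrasts.** The tables in SAP section 10 (Days Of Therapy) are headed "Among admissions with an included antibiotic, by hospital". Table 3 there reads "For 3 contrasts (PAR vs Historical year; Res/PreA vs historical Year; PAR vs Res/PreA", and lists a difference in the proportion using each drug and a difference in mean DOT, each with a 95% interval and no period term. SAP section 13 repeats the layout for ICU admission and total hospital days. Death is to be summarised in the same set of tables, but no difference is listed for it.

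**Order and dates.** Under SAP 3.2, two hospitals (102 and 373 beds) ran Res/PreA then PAR, and two (220 and 274 beds) ran PAR then Res/PreA. SAP section 6 prints the periods as "Study period 1 (October 6, 2014 through April 3, 2014" and "Study period 2 (May 4, 2015 through October 30, 2014". As printed, each ends before it begins. I read both end years as 2015.

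**Purpose of the crossover.** Protocol section 4 says the order was reversed in half the hospitals "to help alleviate the concern for seasonal/temporal effects when comparing the strategies to each other". SAP 3.5.2 says where that helps: "The crossover nature of the trial design helps to alleviate this bias inherent to comparing the AS interventions in pooled analyses".

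**Models.** SAP section 10 plans one DOT model per antibiotic with hospital, study period, strategy, calendar time and demographics, and will explore three interactions. Protocol 9.4.1.3 describes a model with fixed treatment and period effects and random site and period-by-site effects, introduced as a way to explore site heterogeneity.

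**The concern.** A single hospital contributes one period under each strategy. Its PAR minus Res/PreA difference is therefore also a period difference, and here largely a cold-season versus warm-season difference. The interval in Table 3 reflects patient sampling only. More patients make it narrower around strategy plus period, not around strategy.

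The design protects against this only when hospitals with opposite orders are combined, as SAP 3.5.2 recognises. The contrasts that the SAP sets out with intervals are the ones without that protection. The error would also be hard to recognise: a common period effect has opposite signs in the two order groups, so it resembles the pharmacist-driven site variation that both documents expect.

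DOT and patient outcomes form a separate planned report (SAP section 1). Protocol section 10 says the findings may help decide whether later research is limited to one intervention.

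**Working it through.** **Inputs.** Order and bed sizes: SAP 3.2. Dates: SAP section 6, end years read as 2015. Sample size, proportions and alpha: protocol 9.1. The documents give no seasonal or period effect, so the shifts below, and the n of 1000, are assumptions.

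**1. The protocol's power figure.** With 3000 patients per period, 0.50 vs 0.55, two-sided alpha 0.05:
- Null SE = √(2 × 0.525 × 0.475 / 3000) = 0.01289
- Alternative SE = √((0.25 + 0.2475) / 3000) = 0.01288
- Power = Φ((0.05 − 1.96 × 0.01289) / 0.01288) = Φ(1.92) = 0.973

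This reproduces the stated 97%, so the protocol's power statement is for a within-hospital comparison of the two periods.

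**2. Aliasing within one hospital.** There are two cells, (period 1, first strategy) and (period 2, second strategy). Intercept + strategy + period has 3 columns and rank 2, so strategy and period cannot be separated at any sample size. Each period lasts 180 days, with 30 days between them. They share 25 calendar dates, all in October.

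**3. Sign pattern.** Let d be the period 2 minus period 1 shift, common to all hospitals, with no strategy effect.

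| Hospital | Order | PAR minus Res/PreA |
|---|---|---|
| 102 beds | Res/PreA, PAR | +d |
| 220 beds | PAR, Res/PreA | −d |
| 274 beds | PAR, Res/PreA | −d |
| 373 beds | Res/PreA, PAR | +d |

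**4. Size at one hospital.** Take a binary outcome with 0.50 in one period, 0.50 + d in the other, and no strategy effect. The probability that the 95% interval excludes zero is Φ(d/SE − 1.96) + Φ(−d/SE − 1.96), with SE = √((0.25 + (0.5 + d)(0.5 − d)) / n).

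| Assumed d | n = 3000 per period | n = 1000 per period |
|---|---|---|
| 0.01 | 0.12 | 0.07 |
| 0.02 | 0.34 | 0.15 |
| 0.03 | 0.64 | 0.27 |
| 0.05 | 0.97 | 0.61 |

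The interval half-width is about 0.025 at n = 3000 and 0.044 at n = 1000. The smaller n is shown because Table 3 is limited to admissions with an included antibiotic. The last row at n = 3000 is the protocol's 97% again: a 0.05 period shift is declared as often as a true 0.05 strategy difference.

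**5. Combining hospitals.** Over the 8 hospital-period cells, hospital + period + strategy has 6 columns and rank 6, so strategy is estimable. A common d gives a strategy coefficient of 0. Pooling the hospital differences without a period term gives (1 − 1 − 1 + 1)d/4 = 0 with equal weights, and (102 − 220 − 274 + 373)d/969 = −19d/969 ≈ −0.02d with bed-size weights.

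**6. Interactions.** Adding hospital × period as fixed effects gives 9 columns and rank 8. The model then has a free period shift for each hospital, and strategy is not estimable. Fixed hospital × strategy (rank 8 of 9) and period × strategy (rank 6 of 7) also leave the design rank-deficient, so the meaning of the strategy coefficient would depend on the coding. The protocol's random period-by-site term avoids the first problem.

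**The case against.** The strongest reply is that the period-adjusted analysis already exists. The SAP section 10 model contains hospital, study period and strategy, is planned without conditional wording, and has the intervention effect on DOT as its purpose. Protocol 9.4.1.3 describes a comparable model for outcomes in general. A reader who sees only the sentence on stratified pooling might infer that period adjustment is merely optional, or that the crossover's protection goes unused. The documents do not support that, least of all for DOT. Nor do they decline to pool: site variation is given as the reason to look at sites separately, and pooling is allowed in the next sentence.

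Three further points stand. These are secondary analyses of a feasibility study whose primary analysis is descriptive. SAP 3.5.2 openly accepts that temporal effects may differ between the periods. And the by-hospital tables show period and order, so an alert reader could notice the alternating signs.

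The reply does not reach the contrasts themselves. Table 3 is where PAR vs Res/PreA and its interval are specified, and it is unadjusted. Neither model is named as the source of that estimate. SAP section 13 has no model, so for hospital days, ICU admission and death the SAP relies on the unadjusted tables. A stated limitation does not re-centre an interval.

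**Conclusion.** The point holds and should be fixed, at moderate severity. The by-hospital PAR vs Res/PreA differences in SAP Table 3 estimate strategy plus or minus period, with the sign set by the order. The aliasing is exact and needs no assumption about season. Calling it cold versus warm season depends on reading the misprinted end years as 2015, and the two periods share 25 October dates.

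The size is conditional. At the protocol's 3000 per period, assumed shifts of 0.01 to 0.05 give a single hospital a spurious exclusion of zero with probability 0.12 to 0.97, and at 1000 per period 0.07 to 0.61. A reader might go further and assume, say, use 5–15% above the yearly mean in winter and as far below it in summer, which implies a site-level bias of 10–30%. No seasonal figure in the documents supports that. Seasonal change in the number of infections or admissions also need not carry over one for one to outcomes measured per treated admission.

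Nor is the pooled estimate unbiased in every case. Its zero bias requires a period effect common to the hospitals. Drug shortages that affected hospitals differently would break that condition. The primary feasibility summaries are not affected.

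**What to change.** In SAP 3.5, 10 and 13:

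- Name the pooled hospital + period + strategy model as the reported PAR vs Res/PreA estimate for DOT, total hospital days, ICU admission and death. For DOT this means designating the model already planned; for the other three it means adding one to section 13.
- Keep the by-hospital contrasts, labelled descriptive and aliased with period. They could also be shown season-matched: each hospital's period 2 minus period 1 change, less the change between the same calendar dates in its historical year. The historical year covers every date needed, although 6–30 October 2013 would serve both windows. This removes recurring seasonality only, not the drug shortages.
- State that hospital × period will not be a fixed effect beside strategy, and take it as random as in protocol 9.4.1.3. Say how the other two interactions will be coded and read.
- State how the interval for the pooled estimate is obtained.
- Correct the end years in SAP section 6.

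This costs SAP wording and some programming, with no new data. The main downside is precision. A cluster-level estimate has 4 hospital differences less 2 order means, or 2 degrees of freedom, so its interval would be wide. The estimate also rests on the common-period assumption, which should be stated beside the result.
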